### **12.4 Definition of Suspected Unexpected Serious Adverse Reactions**

Protocol No: 2013-002574-49

Date 09 September.2015

Version: 03

Each SAE that is at least possibly related to IMP is to be classified by the investigator as expected or unexpected. A SAE that is at least possibly related to IMP, and **unexpected**, is defined as a Suspected Unexpected Serious Adverse Reaction (SUSAR). It is expected if it is already known from earlier trials or is mentioned in relevant documents. The reference security information of the IMP can be found in the approved SPC (122).

## **12.5 Assessment of Adverse Events**

AE is assessed at each clinician visit (including 3 months follow up), and via telephone assessments (12 months and 5 years) and in the treatment platform. If any AE is recorded in the treatment platform, the therapist will print out the information and give it to the investigator.

### **12.5.1 Assessment of Intensity**

Each AE is to be classified by the investigator as mild, moderate or severe.

**Mild:** Acceptable. The subject is awareness of symptoms or signs, but they are easy tolerated.

**Moderate:** Disturbing. The AE is discomfort enough to interfere with usual daily activity.

**Severe:** Unacceptable. The subject is incapacity to work or to do usual daily activities.

### **12.5.2 Assessment of Causality**

**Unlikely:** The event is most likely related to an etiology other than the IMP.

**Possible:** A causal relationship is conceivable and cannot be dismissed.

**Probably:** Good reason and sufficient documentation to assume a causal relationship.

## **12.6 Methods for Eliciting Adverse Events**

Safety measurements performed for each clinician visit and telephone assessments (3 months, 12 months and 5 years) (as indicated in "Investigational schedule").

## **12.7 Reporting of Adverse Events**

### **12.7.1 Reporting of Adverse Events**

All AEs will be recorded on a separate AE form in the CRF.

### **12.7.2 Reporting of Serious Adverse Events**

SAEs will be reported by the investigator and sent the principle investigator immediately.

Follow-up information describing the outcome of the SAE and action taken will be reported as soon as it is available. The original SAE form must be filed with the CRF.

### **12.7.3 Reporting of Suspected Unexpected Serious Adverse reactions**

The sponsor must report all SUSARs that resulted in death or was life threatening to The Norwegian Medicines Agency; NOMA within 7 days. Other SUSAR should be reported within 15 days. In addition will the sponsor report all SUSAR to all Principal Investigators involved in trials with the IMP.

## **12.8 Follow-up of Adverse Events**

The investigator must ensure that follow-up of the participant is appropriate to the nature of the event, and that it continues until resolution. Any change in terms of diagnosis, intensity, seriousness, measures taken, causality or outcome regarding adverse events must be written up in an Adverse Events evaluation form.

## 13. Statistics and Data Management

### 13.1 Statistical Analysis

Statistical analysis will be performed by the investigator and specially designated collaborators and quality controlled and cross-checked by independent party

The primary objective is to demonstrate superiority of concentrated ERP + DCS vs. concentrated ERP + placebo at significance level of  $< 0.05$  (5%). Data will basically be analyzed using intention to treat methodology with a mixed models design, accounting for missing data, with relevant covariates for a given analysis. Data will primarily be analyzed employing multivariate methods (ANOVAs/MANOVAs) with repeated measurement.

Covariates are described in the moderator section (Chapter 6.5). Missing data will be replaced (multiple imputation methods). There will be calculations of effect sizes (Cohen's effect size) for all primary and secondary endpoints. Other relevant multivariate statistical analyses will be performed if relevant to elucidate results of importance to the objectives of the study. Safety data (e.g. side effects) will be collected and summarized in the study results.

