### 6.3 Predictors

The following variables will be employed as predictors of outcome: the patients' evaluation of the credibility of the treatment (73), presence of comorbidity (74, 75), number of previous

treatments, treatment motivation as well as the onset, duration and severity of the disorder. For description of instruments, see section 7. For assessment points see Table 1 in the Appendix.

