#### **6.5 Descriptives**

Please note that patients in the current trial are entitled to treatment in the Norwegian specialist health care, and that the questionnaires listed below are part of standard diagnostic and assessment procedures in the OCD-team in Helse-Bergen, and are approved as part of the current trial by the Regional Committee of Ethics (2013/195/REK Sør-Øst- D). The following are routinely measured: sleep disturbances (77); the patients' beliefs about the stability of the condition (78); stable personality characteristics (79); sensitivity to sensory and external stimulation (80); and Behavior Rating Inventory of Executive Function – Adult Version (82). For description of instruments, see section 7. For assessment points see Table 1 in the Appendix.

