### 11.2 Treatment Assignment/ Randomization

Patients are upon inclusion randomly assigned to DCS or placebo using a 2:2:1 ratio of 250 mg DCS: 100 mg DCS: placebo. In order to control for potential interaction effects with antidepressants (121), patients will be stratified on current anti-depressive medication or not. Within each subgroup patients will be randomized in blocks of 5 into ERP+DCS 100 mg, ERP+DCS 250 mg, or ERP + Placebo in the proportions 2:2:1.

A research unit at Karolinska Institute, Sweden, which is not involved in the study, will be responsible for the randomization. Randomization lists will be sent directly to Kragerø pharmacy that will be responsible for providing the medication for patients enrolled.

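### Section 13.1 takes its covariates from a moderator section that does not exist, names neither baseline Y-BOCS nor the antidepressant stratum, and calls primary an ANOVA/MANOVA in which T0 is a repeated level

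*Protocol*

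**What the plan says.** Four parts of the Protocol bear on this.

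- **Covariates.** Section 13.1 provides for a mixed model "with relevant covariates for a given analysis" and then says where the list is: "Covariates are described in the moderator section (Chapter 6.5").
- **What is there.** That chapter is headed "6.5 Descriptives". It opens its list with "The following are routinely measured: sleep disturbances (77") and goes on to illness beliefs, "stable personality characteristics (79); sensitivity to sensory and external stimulation (80") and executive function. Section 6.3 is Predictors and 6.4 is Mediators; no section is headed moderators.
- **Stratification.** Under section 11.2, "patients will be stratified on current anti-depressive medication or not". Sections 10 and 11.2 both give a possible interaction between DCS and antidepressants as the reason.
- **Model.** Section 4 makes the assessment points the repeated factor and counts T0 among them. Section 13.1 names a mixed model that accounts for missing data, then says "Data will primarily be analyzed employing multivariate methods (ANOVAs/MANOVAs) with repeated measurement", then adds multiple imputation.

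**The concern.** A statistician who follows the cross-reference arrives at descriptive questionnaires. The two covariates with the best claim to be in the primary model, the baseline value of the outcome and the randomisation stratum, are not on that list. Stratified randomisation balances antidepressant use across arms. It does not estimate or remove an interaction; only a model term does that, and no interaction test is named.

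The method sentences also compete. A repeated-measures ANOVA/MANOVA with T0 as a level and a mixed model can give different primary p-values, and the text does not say which governs. With T0 as an outcome, the arm-by-time contrast from T0 to a follow-up is a change-score comparison, which is less precise than adjusting for baseline. With only 32 placebo patients planned, precision matters.

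**Working it through.** **Inputs from the Protocol.** Section 13.2: d = 0.50, alpha 0.05 (sidedness not stated), 80% power, arms of 64, 64 and 32. The scale of d is not given.

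**Assumed, because the Protocol gives no figure.** Two-sided test; equal SD at T0 and follow-up; correlation rho between T0 and follow-up Y-BOCS of 0.3 to 0.7; stratum explaining 1% to 10% of outcome variance; 30% to 70% of patients on antidepressants.

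**The plan's own figure.** By the normal approximation, 64 v 64 at d = 0.50 gives 80.7% power, so 64 is the equal-arm size. Against 32 placebo patients, unadjusted two-sided power is 63.7% for one dose and 71.6% for both doses pooled. That shortfall is a separate matter, and nothing below depends on it.

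**Variance.** In units of the follow-up SD:

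- change from baseline: variance 2(1 - rho)
- baseline as covariate: variance 1 - rho²
- adjusted relative to change: (1 - rho²) / [2(1 - rho)] = (1 + rho)/2

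The change contrast therefore has 1/0.65 = 1.54, 1/0.75 = 1.33 and 1/0.85 = 1.18 times the adjusted variance at rho 0.3, 0.5 and 0.7. The ratio (1 + rho)/2 is below 1 for every rho below 1, so adjustment never loses in this comparison.

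**Power if d = 0.50 is on the follow-up score.** For 128 v 32, SE = sqrt(1/128 + 1/32) = 0.1976 and power = Φ(0.50/(SD × 0.1976) - 1.96), with SD the square root of the variance above. For 64 v 32, SE = sqrt(1/64 + 1/32) = 0.2165.

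| rho | SD change / adjusted | 128 v 32: change v adjusted | 64 v 32: change v adjusted |
|---|---|---|---|
| 0.3 | 1.183 / 0.954 | 57.1% v 75.6% | 49.7% v 67.8% |
| 0.5 | 1.000 / 0.866 | 71.6% v 83.2% | 63.7% v 76.0% |
| 0.7 | 0.775 / 0.714 | 90.4% v 94.3% | 84.6% v 89.9% |

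**Power if d = 0.50 is on the change scale.** For 128 v 32, unadjusted power is 71.6% at any rho. Adjustment raises the standardised effect to 0.50/sqrt((1 + rho)/2) = 0.620, 0.577 and 0.542. Power is then Φ(0.620/0.1976 - 1.96) = 88%, Φ(0.577/0.1976 - 1.96) = 83% and Φ(0.542/0.1976 - 1.96) = 78%.

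**Stratum alone (64 v 32).** The SD becomes sqrt(1 - R²). Power goes from 63.7% to 64.1% at R² = 0.01 and 68.2% at R² = 0.10, a gain of about 0.5 to 4.5 points.

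**Interaction.** SE = sqrt[(1/32 + 1/n)(1/p + 1/(1 - p))], where n is 64 or 128 and p is the share on antidepressants. For an interaction of 0.5 SD, power runs from 18% (n = 64, p = 0.3 or 0.7) to 24% (n = 128, p = 0.5). The interaction detectable with 80% power is about 1.1 to 1.3 SD.

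**The case against.** The best defence is that section 13.1 leaves relevant covariates and other relevant analyses open, that section 6.3 lists severity among the predictors ("as well as the onset, duration and severity of the disorder"), and that a list of model terms usually belongs in a statistical analysis plan, which is not at hand. This stands in part. The Protocol excludes neither covariate, and nothing forces the section 6.5 questionnaires into the primary model. But section 13.1 does not cite 6.3, and a reference to a section that does not exist is an error on the page, not a detail deferred.

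A reader might infer two stronger points that the document does not support.

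- *The antidepressant interaction will never be tested.* No test is named, but none is ruled out, and a separate plan may specify one.
- *ANOVA/MANOVA will discard every patient with a missed visit.* Section 13.1 prescribes intention to treat, a mixed model that accounts for missing data, and multiple imputation. After imputation no patient is dropped.

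The power figures are also open to challenge. The scale of d is not stated, and the primary endpoint is a change in Y-BOCS. Rho is assumed. A group-by-time MANOVA over several visits is a test with several degrees of freedom, not the single contrast computed here. A mixed model that keeps T0 as an outcome but constrains baseline means to be equal would avoid the loss, and the mixed-model wording permits it. All of this stands. It makes the size of the loss conditional; it does not change its direction or settle which method is primary.

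**Conclusion.** The point holds in this form. The covariate reference is wrong. The section it leads to contains neither baseline Y-BOCS nor the stratification factor. No analysis counterpart is named for the interaction that motivated the stratification. The paragraph calls ANOVA/MANOVA primary while also naming a mixed model.

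Read literally, with T0 as a repeated level, the treatment contrast carries 1.18 to 1.54 times the variance of a baseline-adjusted one for rho from 0.7 down to 0.3. With d = 0.50 on the follow-up score, that costs about 4 to 18 power points for pooled DCS v placebo and about 5 to 18 for one dose v placebo. With d on the change scale, unadjusted pooled power stays at about 72% and adjustment still gains precision. These sizes rest on an assumed rho, a two-sided test and a single follow-up contrast. The case for naming the stratum is agreement between randomisation and analysis more than power. The plan should be corrected, but the fault does not invalidate the trial.

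**What to change.** In section 13.1:

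1. Delete the reference to chapter 6.5 and name the covariates.
2. State one primary model for continuous Y-BOCS in place of ANOVA/MANOVA: a likelihood-based mixed model for T1-T3 with arm, visit, arm-by-visit, T0 Y-BOCS (by visit) and antidepressant stratum. Keep multiple imputation as a sensitivity analysis. The 5-year data are already to be analysed separately under section 11.7.
3. Keep a method for the categorical primary endpoints of sections 6.1.1 and 6.1.2. Adjust the response, remission and diagnostic-status analyses for T0 Y-BOCS and stratum too, so that replacing the ANOVA/MANOVA sentence does not leave them uncovered.
4. Name the DCS-by-antidepressant interaction as exploratory and report it with its confidence interval, stating that power is low (about 18% to 24% at 0.5 SD under the assumptions above).

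The cost is wording and analysis code. Table 1 already schedules T0 Y-BOCS for every patient, and antidepressant status has to be known in order to randomise. No new data and no change to sample size are needed.

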#### *Handling of missing data and drop-outs.*

Since the treatment is concentrated over a short number of days, the drop-out rates are, based on our experiences expected to be very low (so far, no patients have dropped out from the intensive treatment). Missing data will be handled by standard procedures.

### 13.2 Determination of Sample Size

A meta-analysis by Norberg, Krystal & Tolin [69] found a medium effect size for ERP + DCS for heterogeneous samples of OCD-patients. However, in the current study, only patients who have relapsed after an initially successful ERP-treatment will be included. This is a sample which supposedly increases the possibility to detect DCS-effects and we assume that the effect size would be larger than that found in previous studies. In order to have 80% power to detect a moderate effect size ( $d = 0.50$ ) at an alpha-level of 0.05 a total of 160 patients will be included (64 in each of the DCS-conditions and 32 in the Placebo group). Patients lost or withdrawing from the study will be treated as drop-outs and replaced. We estimate an increased sample size of 10 patients, in total, to compensate for possible drop-outs.

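### The 80% power in Section 13.2 does not hold for a two-sided, unadjusted DCS-versus-placebo comparison at 64/64/32, and the section names neither the contrast nor the sidedness

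*Protocol*

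**What the plan says.** Section 13.2 opens its calculation with "In order to have 80% power to detect a moderate effect size", gives that effect as d = 0.50 and alpha as 0.05, and continues "a total of 160 patients will be included (64 in each of the DCS-conditions and 32 in the Placebo group". It adds 10 patients in total for drop-outs and says that drop-outs are replaced.

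Section 11.2 agrees with this split: patients are "randomly assigned to DCS or placebo using a 2:2:1 ratio of 250 mg DCS: 100 mg DCS: placebo", in blocks of 5 within antidepressant strata.

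Section 13.1 names the objective: "The primary objective is to demonstrate superiority of concentrated ERP + DCS vs. concentrated ERP + placebo at significance level" of 5%. On the analysis it says "Data will primarily be analyzed employing multivariate methods (ANOVAs/MANOVAs) with repeated measurement", within an intention-to-treat mixed-model framework with relevant covariates.

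None of these sections says whether the doses are pooled or tested separately, whether the test is one- or two-sided, or what correlation between repeated measures was assumed.

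**The concern.** For d = 0.50, two-sided 5% and 80% power, the standard equal-arm answer is 64 per group. Section 13.2 gives 64 to each DCS arm but only 32 to placebo, and placebo is the arm that every DCS-versus-placebo comparison depends on. The 80% therefore looks like an equal-arm figure attached to an unequal design.

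The power statement is the justification for 160 patients. If it does not apply to the primary objective, a null result may be read as having had a 20% chance of missing d = 0.50 when, under the simple test, that chance was larger.

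**Working it through.** **Inputs.** d = 0.50, alpha 0.05, target power 80% and arms of 64/64/32 (Section 13.2); 2:2:1 allocation (Section 11.2); DCS versus placebo (Section 13.1). Sidedness is not stated. It is taken as two-sided because the F tests of the planned ANOVA/MANOVA are non-directional; one-sided is also shown.

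**Method.** Two-sample t-test with non-centrality ncp = d × √(n1·n2/(n1+n2)) and n1+n2−2 degrees of freedom. Power comes from the non-central t distribution. A hand check is Φ(ncp − 1.96).

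**Reproducing the stated 80%.** For 64 v 64, ncp = 0.5 × √(4096/128) = 2.83 and power is 80.1%. With 63 per arm it is 79.5%, so 64 is the smallest equal-arm size that reaches 80%. In this trial the only 64 v 64 pair is 250 mg against 100 mg.

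**The DCS-versus-placebo comparisons, two-sided 5%.**

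| Comparison | n1·n2/(n1+n2) | ncp | Power (t) | Normal check |
|---|---|---|---|---|
| One dose v placebo, 64 v 32 | 2048/96 = 21.33 | 2.31 | 62.8% | 63.7% |
| Pooled v placebo, 128 v 32 | 4096/160 = 25.6 | 2.53 | 71.0% | 71.6% |
| One dose, all 10 extras kept, 68 v 34 | 2312/102 = 22.67 | 2.38 | 65.5% | – |
| Pooled, all 10 extras kept, 136 v 34 | 4624/170 = 27.2 | 2.61 | 73.7% | – |

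The last two rows are generous: the extras are meant to offset losses, and Section 5 caps inclusion at 160.

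**Three-group F test, both doses at d = 0.50, 64/64/32.** Power is 60.5%.

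**One-sided 5%.** Pooled (128 v 32) gives 80.9%; one dose (64 v 32) gives 74.1%.

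**Effect detectable with 80% power, two-sided.** d = 0.56 pooled and d = 0.61 per dose.

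**Size needed for 80% at d = 0.50 and 2:2:1, two-sided.** 200 patients pooled (80/80/40) or 240 per dose (96/96/48).

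**Adjustment for baseline (assumed correlation ρ; the protocol gives none).** The residual SD shrinks by √(1−ρ²), so d is divided by that factor.

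| ρ | One dose | Pooled |
|---|---|---|
| 0.3 | 66.9% | 75.0% |
| 0.4 | 70.3% | 78.3% |
| 0.5 | 75.2% | 82.7% |
| 0.6 | 81.5% | 88.2% |

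Pooled power passes 80% at about ρ = 0.45 (80.4%); one dose does so only near 0.6. Adjustment by simple change scores does not guarantee a gain: at ρ = 0.5 it leaves power at 62.8% and 71.0%, and at ρ = 0.3 it lowers them to 48.9% and 56.6%.

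**The case against.** **A one-sided pooled test fits the design just as well.** With 2:2:1 in blocks of 5, 31 placebo patients (total 155) give 79.8% and 32 (total 160) give 80.9%, so 160 is the smallest complete-block total reaching 80%. The hypothesis in Section 3 is directional and Section 13.1 speaks of superiority. This stands as far as it goes: the number 64 does not prove that an equal-arm calculation was used. But no one-sided test is stated, the planned ANOVA/MANOVA does not fit one, and one dose against placebo reaches only 74.1% even so.

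**A different effect-size scale might lie behind the number.** A three-group F test at Cohen's f = 0.25 needs 158 patients. Section 13.2 states d, however, not f. With both doses at d = 0.50 and arms of 64/64/32, the non-centrality is 6.4, so f = √(6.4/160) = 0.20.

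**The planned analysis is more efficient than a t-test.** This also stands. Section 13.1 foresees repeated measures and covariates, and at a moderate correlation the pooled comparison would reach 80%. It limits the consequence but does not rescue the statement, because Section 13.2 does not rest its 80% on any such gain.

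**Details may be left to a statistical analysis plan.** Sidedness and pooling could be. But the protocol itself ties a power figure to arm sizes and an objective, and it is that tie which fails.

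**Dose against dose is of interest too.** Section 3 calls the dose-response evidence inconclusive and Section 4 makes dose a between factor. It is still not the primary objective.

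**Conclusion.** The stated 80% is not supported for the DCS-versus-placebo objective. Under a two-sided 5% unadjusted comparison at d = 0.50, power is 71% pooled and 63% per dose, a shortfall of 9 and 17 percentage points. These figures assume a single-time-point two-sample test and no alpha split between doses; 0.025 for each dose would give about 51% per dose.

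A reader might infer three stronger things that the documents do not support:

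- **That the type II error of the primary analysis is 29–37%.** That holds only for the unadjusted two-sided test. The power of the planned mixed model depends on a correlation that the protocol does not give.
- **That losses by 12 months will lower power further by a known amount.** The protocol gives no 12-month loss rate, expects very little drop-out, replaces drop-outs and adds 10 patients.
- **That the 2:2:1 ratio is itself an error.** It is stated consistently in Sections 11.2 and 13.2 and is a legitimate choice. What is wrong is the power sentence.

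**What to change.** In Section 13.2, name the primary contrast (doses pooled, or each dose against placebo) and state that the test is two-sided. Then do one of the following:

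- restate power at d = 0.50 as about 71% pooled and 63% per dose, or equivalently 80% power at d = 0.56 pooled and 0.61 per dose; or
- keep a higher figure, and state the covariate or repeated-measures correlation and the analysis model that produce it.

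This costs a few sentences and a less favourable stated power. It needs no extra patients and no change to randomisation.

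Equal allocation is an optional design choice, not part of the required fix. The same 160 patients at 1:1:1 would give 84% pooled (107 v 53), but still only 72% for one dose against placebo, and dose against dose would fall from 80% to 72%. It would also need a new randomisation list, and it reaches 80% only if the pooled contrast is made primary.

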| Primary Endpoint:                             | Changes in OCD symptoms from pre-treatment (T0) to post-treatment (T1) as well as 3-months (T2), 12 months (T3) and 5-year follow-up (T4).                                                                                                                                      |
| Efficacy Parameters:                          | Remission in diagnostic status according to the Structured Clinical Interview for DSM-5 Axis I disorders (SCID-I) criteria for OCD and Clinician administered Y-BOCS interview by specially trained and blinded assessors.                                                      |
| Safety Parameters:                            | Adverse Events (AE) and Serious Adverse Events (SAE) assessed during the active treatment days, at post-treatment, 3-months (at clinic), 12 months and 5 years follow-up using telephone clinician assessments.                                                                 |
|                                               |                                                                                                                                                                                                                                                                                 |
| POPULATION OF TRIAL SUBJECTS           |                                                                                                                                                                                                                                                                                 |
| Description of Trial Subjects:                | Patients with a primary diagnosis of OCD according to the DSM-5 who have partially or fully relapsed, or not responded from standard ERP-treatment delivered by trained therapists.                                                                                             |
| Number of Subjects:                           | 160 patients with OCD                                                                                                                                                                                                                                                           |

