## 5. Inclusion and exclusion criteria, withdrawal

All 15 OCD-teams in Norway refer patients to the study, thus providing nationwide coverage of relapsed or non-responsive OCD patients.

A maximum of 160 patients will be included (see p.31 for power calculations) within the period from October 2015- June 2018.

Through the National OCD-implementation project all OCD-patients in Norway are ensured access to evidence based treatment. Standardized procedures for collection and storage of data (quality databases) are also established. These data will serve as reference data for standard treatment response, as well as provide detailed information regarding the first treatment-course for the relapsed OCD-patients.

The inclusion procedure implies that all relevant patients in Norway in the given time period will be offered participation. If this population turns out to be fewer than 160 patients during the study period, the inclusion period might be extended six months. If less than 160 patients are included at that point, analyses will be performed on the number of patients included by the end of the study period.

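### Section 5 caps inclusion at 160, but Section 13.2 uses all 160 for power and then adds 10 patients and replacements, which the cap leaves no room to enrol

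*Protocol*

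**What the plan says.** All references are to the protocol.

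- **Section 13.2** aims for a power of 80% when d is 0.50, testing with a 5% alpha, and gives the size as follows: "a total of 160 patients will be included (64 in each of the DCS-conditions and 32 in the Placebo group". It then says that patients who are lost or withdraw count as drop-outs and are replaced, and closes with "We estimate an increased sample size of 10 patients, in total, to compensate for possible drop-outs".
- **Section 5** refers to that power calculation and states "A maximum of 160 patients will be included". It uses 160 twice more: recruitment may be extended by six months if fewer than 160 are found, and if the number is still short, those included are analysed.
- **The Protocol Summary** gives the number of subjects as "160 patients with OCD".
- **Section 13.1** plans intention-to-treat analysis with mixed models and multiple imputation. Its paragraph on missing data and drop-outs expects very low drop-out because "so far, no patients have dropped out from the intensive treatment".
- **Section 11.7** excludes from the study a patient who decides not to take the capsule on Day 2.

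**The concern.** The 160 in Section 13.2 is the number before any allowance for drop-out. Adding 10 gives 170, and the replacement rule could take it further. Section 5 forbids both once 160 patients are in. Whoever runs recruitment therefore has two instructions that cannot both be followed, and the protocol does not say which prevails.

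The planned size and the point at which recruitment stops belong in the protocol. Section 5 ties its extension rule and its short-sample rule to the same figure. If the cap prevails, the allowance meant to protect the power statement is void. If Section 13.2 prevails, a stated maximum is exceeded.

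The only support given for low drop-out concerns the four-day treatment. The hypothesis in Section 3 places the expected differences at the follow-ups, and no rate of loss to follow-up is given.

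**Working it through.** **Inputs.** d = 0.50, alpha 0.05, target power 80%, and arms of 64, 64 and 32 (Section 13.2); allocation 2:2:1 in blocks of 5 (Section 11.2); allowance 10 (Section 13.2); maximum 160 (Section 5). Sidedness is not stated. Section 13.1 says only "The primary objective is to demonstrate superiority of concentrated ERP + DCS vs. concentrated ERP + placebo", so both versions are shown.

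**Enrolment arithmetic.**
- 64 + 64 + 32 = 160, so the 160 contains no allowance.
- 160 + 10 = 170. At 2:2:1 this is 170 × 2/5 = 68 per DCS arm and 170/5 = 34 on placebo. The allowance is 10/170 = 5.9%.
- 170 − 160 = 10 patients above the maximum in Section 5.
- If the 10 were meant to sit inside the 160, the base would be 150, or 60/60/30. Section 13.2 gives 64/64/32, so that reading fails.
- 160/5 = 32 and 170/5 = 34 are both whole numbers, so the block size does not settle which total is meant.

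**Power formula.** Two-sample t-test with noncentrality d × √(n1·n2/(n1 + n2)) and n1 + n2 − 2 degrees of freedom.

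**Reproducing the protocol's figure.** Two routes reach it, both without drop-out:
- 64 v 64, two-sided: 0.50 × √32 = 2.83, power 80.1%. This yields 64 per arm, but it is not a comparison with the 32 placebo patients.
- 128 pooled DCS v 32 placebo, one-sided 5%: 0.50 × √25.6 = 2.53, power 80.9%.

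**Effect of the conflict.** Take 10 patients who contribute no data, spread over the arms in the allocation ratio. With 170 randomised, 160 remain; under the cap, 150 remain.

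| Patients contributing | Pooled DCS v placebo | Noncentrality | Two-sided | One-sided | One dose v placebo | Two-sided |
|---|---|---|---|---|---|---|
| 150 | 120 v 30 | 0.50 × √24.0 = 2.45 | 68.2% | 78.6% | 60 v 30 | 59.9% |
| 160 | 128 v 32 | 0.50 × √25.6 = 2.53 | 71.0% | 80.9% | 64 v 32 | 62.8% |
| 170 | 136 v 34 | 0.50 × √27.2 = 2.61 | 73.7% | 83.0% | 68 v 34 | 65.5% |

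The difference between 160 and 150 is 71.0 − 68.2 = 2.8 points (pooled, two-sided), 80.9 − 78.6 = 2.3 points (pooled, one-sided) and 62.8 − 59.9 = 2.9 points (per dose, two-sided).

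**The case against.** The strongest reply is that this is a matter of wording with little statistical effect. Much of that stands.

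- **Only Section 5 is a cap.** A reader might infer that 160 is a ceiling in two places. The Summary entry is a planned number and sets no maximum.
- **No analysed number is stated.** A reader might infer that any loss takes the trial below the number its power needs. Section 13.2 speaks of patients included, and Section 13.1 plans intention to treat with multiple imputation, so a patient lost to follow-up stays in the analysis. The inference holds only for patients removed outright, such as those under Section 11.7, and in part for missing outcomes, which still cost information.
- **The low power values have another cause.** A reader might blame the conflict for power of 60% to 68%. With all 160 patients present, two-sided power against placebo is already 71% pooled and 63% per dose. That shortfall comes from the small placebo arm under 2:2:1 allocation and from the unstated sidedness.
- **160 was never guaranteed.** Section 5 accepts analysis of a smaller sample if recruitment falls short.
- **Some links are inferred.** Section 13.2 does not derive the 10, so its dependence on treatment-phase experience is not documented. Section 11.2 does not give the length of the randomisation list, so an effect on that list cannot be asserted.

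None of this removes the contradiction. No section says that the extra 10 or the replacements fall outside the maximum, and no reading lets all the figures stand together.

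**Conclusion.** The point holds as an inconsistency in the enrolment figure. 64 + 64 + 32 is added correctly, but the cap in Section 5 cannot be combined with the allowance and replacement rule in Section 13.2.

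If 10 patients contribute no data and cannot be made up, the cost is about 2 to 3 power points. In the one-sided pooled reading this moves power from just above 80% to just below it (80.9% to 78.6%). In the two-sided reading power against placebo is below 80% either way. These figures assume d = 0.50, a simple two-group t-test and losses spread in the allocation ratio. They overstate the cost where patients lost to follow-up still contribute some data.

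The documents do not support the stronger conclusion that the cap by itself makes the trial seriously underpowered. The correction is worth making because recruitment needs one stopping figure.

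**What to change.** Use one enrolment figure in the Summary, in Section 5 (including its extension and short-sample triggers) and in Section 13.2. Either:

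1. randomise up to 170 (68/68/34) and delete the maximum of 160; or
2. keep 160 and delete the 10-patient allowance.

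Under either option, delete the replacement rule in Section 13.2, because replacement alone would breach a maximum. State that all patients are analysed as randomised, and reconcile the exclusion in Section 11.7 with that.

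Then state the sidedness and restate power against placebo, both for the chosen number and for the number expected with 12-month data. At 160, two-sided, that is about 71% pooled and 63% per dose, not 80%.

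**Cost.** The change is one of wording, and the 10 extra patients are already foreseen in Section 13.2. The stated power becomes less favourable. Under Section 15.1, a change to the maximum must be reported to the ethics committee if it requires the committee's approval.
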